### Planned statistical analyses

#### Descriptive statistics

Demographic data (e.g., age, gender, disease, co-morbidities) will be described for the total group and for the subgroups separately. Continuous variables will be denoted with means, standard deviations, and medians. Categorical variables will be denoted in numbers and percentages. The participants included in the 3 arms will be tested on differences between characteristics, with chi-square, ANOVA (Kruskal Wallis).

If variables differ between groups, with a p-value ≤0.10, they will be considered to be potential confounders in further analysis.

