### Study design

The study is designed as a cluster randomised controlled trial with GP practices as the unit of randomisation. To compare the whole intervention with both usual care and SSP only (to isolate the effect of the tool), the trial has three arms: the use of a monitoring and feedback tool embedded in the SSP (group 1), the SSP without the tool (group 2), and usual care (group 3). The CONSORT flowchart (Figure 
1) summarises the trial design. The population consists of 120 participants with COPD and 120 participants with DM2 from 24 GP practices. Each practice provides 5 COPD patients and 5 DM2 patients, which makes a total of 40 patients with COPD and 40 patients with DM2 from 8 practices per trial arm.

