#### Data analysis for primary and secondary outcomes

An intention to treat analysis and a per protocol analysis will be conducted. For each outcome measure (all outcomes are continuous) data will be expressed as mean +/-SD. The between group comparisons will be analysed with multilevel analysis to account for the dependency of observations. We will apply a 3 level linear mixed model (time, participant, practice); the level of statistical significance will be set at 0.05 (two-tailed). Separate models (random intercept) will be set up for each outcome measure. The independent variables in each model are two dummy variables indicating the group, with the group of patients receiving usual care as the reference category and two dummy variables for time and their interaction effects. In addition, an extra dummy variable will be included to indicate the patient group (COPD versus DM2), to study whether the effects in COPD patients differ from the effects in patients with DM2. If needed, additional baseline variables will be included to account for possible confounding. If normality assumptions are violated, outcome variables will be log-transformed and if necessary non-parametric tests will be used. SPSS, version 19 and Mlwin, version 2.02 will be used to analyse the data.

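### Potential confounders are picked by baseline tests at p≤0.10 that ignore practice clustering, which leaves the adjustment set data-driven and open to choice after results are seen

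*Protocol article*

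**What the plan says.** The Descriptive statistics section sets a two-step rule. First: "The participants included in the 3 arms will be tested on differences between characteristics, with chi-square, ANOVA (Kruskal Wallis"). Then: "If variables differ between groups, with a p-value ≤0.10, they will be considered to be potential confounders in further analysis". The candidate list is open-ended: "Demographic data (e.g., age, gender, disease, co-morbidities) will be described for the total group and for the subgroups separately".

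The section on data analysis for primary and secondary outcomes takes this up: "If needed, additional baseline variables will be included to account for possible confounding". Its model has three levels (time, participant, practice) and two group dummies, "with the group of patients receiving usual care as the reference category and two dummy variables for time and their interaction effects". A disease dummy (COPD or DM2) is always included. No other covariate is fixed. Practice size, on which randomisation is stratified, is not named in the model.

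**The concern.** Three features of the rule are unsound.

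- It selects on the wrong property. A baseline p-value measures imbalance between arms, not whether the variable predicts activity. An irrelevant variable can be flagged, and a strong predictor with p>0.10 passed over.
- The tests treat patients as independent. Practices were allocated, the sample size assumes an ICC of 0.10 for activity, and the outcome model has a practice level, yet the selecting tests have none. Their p-values are too small for any characteristic that varies between practices.
- The test spans three arms, while the main comparison is group 1 against group 3. A difference confined to group 2 can trigger adjustment.

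The threshold makes a variable only a potential confounder, and entry then depends on an undefined need. Which model is the primary one can thus be settled after the data, and possibly the results, have been seen.

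**Working it through.** **Inputs from the protocol article.** Threshold 0.10 and the tests (Descriptive statistics). From Study design: "The study is designed as a cluster randomised controlled trial with GP practices as the unit of randomisation", with 24 practices, 8 per arm, and "Each practice provides 5 COPD patients and 5 DM2 patients", so m = 10. From the sample size section: ICC 0.10 for activity, spread 14.6 minutes, difference 10 minutes, 72 per arm, 10% drop-out.

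**Assumptions, not in the document.** Practice ICC of baseline variables 0 to 0.20; 1 to 10 candidate variables; variables jointly explaining R² = 0.1 to 0.3 of the outcome; 14.6 read as a standard deviation.

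**Step 1: the plan's own figure.** With 9 patients in each of 8 practices, the variance of a practice mean is 14.6² × (0.10 + 0.90/9) = 213.16 × 0.20 = 42.63. The standard error of a two-arm difference is √(2 × 42.63/8) = 3.26, and 10/3.26 = 3.06. A two-sided t-test on 14 df then has power 0.813 (0.789 with 8 per practice). So 72 per arm reproduces, and 72/0.9 = 80. The planned sample thus rests on allowing for clustering.

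**Step 2: how often a balanced variable is flagged.** For a continuous or two-category variable, the three-arm test has about 2 df, for which P(χ² > x) = exp(−x/2). The 10% critical value is 4.605. Ignoring practices inflates the statistic by D = 1 + (m − 1) × ICC, so the flag rate is exp(−4.605/(2D)).

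| Covariate ICC | D | Formula | Simulated ANOVA (20,000 runs) |
|---|---|---|---|
| 0 | 1.00 | 10.0% | 10.1% |
| 0.02 | 1.18 | 14.2% | 14.1% |
| 0.05 | 1.45 | 20.4% | 20.1% |
| 0.10 | 1.90 | 29.8% | 30.2% |
| 0.20 | 2.80 | 43.9% | 44.6% |

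With ten independent balanced variables, the chance of at least one flag is 1 − 0.9¹⁰ = 65% without clustering, 90% at ICC 0.05 and 97% at ICC 0.10.

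**Step 3: effect on the treatment comparison.** A single outcome was simulated with no treatment effect (3 arms × 8 practices × 10 patients, outcome ICC 0.10) and analysed by a random-intercept model with a t-test on 21 df, 2,500 runs per row. Simulation error is about ±0.9 points.

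| Covariates, R², covariate ICC | Type I error: none | All pre-specified | Selected at p≤0.10 | Better of none and selected | SE: selected / pre-specified |
|---|---|---|---|---|---|
| 5, 0.1, 0.05 | 5.5% | 5.3% | 5.1% | 6.1% | 0.216 / 0.212 |
| 5, 0.3, 0.05 | 4.7% | 5.7% | 4.3% | 5.8% | 0.198 / 0.185 |
| 5, 0.3, 0.10 | 4.1% | 4.9% | 3.9% | 5.5% | 0.195 / 0.183 |
| 10, 0.3, 0.05 | 4.5% | 4.8% | 3.6% | 5.5% | 0.196 / 0.184 |
| 1, 0.3, 0.05 | 4.6% | 4.8% | 3.6% | 4.9% | 0.195 / 0.183 |

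The rule is neutral to conservative. At R² = 0.3 the standard error is 6% to 7% larger than with pre-specified adjustment; at R² = 0.1 it is about 2% larger.

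**Step 4: the planned model.** There are three time points and two time dummies, so t0 is itself a response. In one simulated data set with complete follow-up, adding a baseline main effect left every group-by-time term unchanged (for example −0.2132, SE 0.1316, both ways). With 10% of follow-up missing, the terms moved by 0.01 or less. The group main effect did move, from −0.2113 to −0.1424. The covariate choice therefore bears on comparisons of arm levels, hardly on differences in change.

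**The case against.** The strongest defence is that the planned model is largely immune. Because t0 is a response, baseline activity is used whatever its balance, and the group-by-time terms barely respond to baseline main effects. Disease is in every model and balanced by design. This stands, and it limits the harm. The 6% to 7% loss of precision comes from the simpler single-outcome model and applies to comparisons of levels.

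A reader might infer three stronger things, none of which the documents support.

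- *That the error rate of the treatment comparison is lost.* The flagging rate is not the type I error of that comparison, which stayed at 3.6% to 5.1% under the rule. The rise to about 6% needs a separate step, choosing between models on their results. The wording on need permits that step but does not prescribe it.
- *That the adjustment set is decided by chance.* Patients agree after being told their practice's allocation (Recruitment of participants; Discussion), so imbalance can be real. Concern about confounding is legitimate here. It argues for naming prognostic variables in advance, since tests that ignore clustering cannot separate selection from chance.
- *That two or three variables would enter the model.* With ten variables, 10 × 0.204 = 2.0 to 10 × 0.298 = 3.0 would be flagged, but both the ICCs and the count are assumed, and a flag is not entry.

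Group and practice are revealed only at the end of the study (Randomisation procedure). That protects data cleaning, but not model choice once the groups are known.

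Nor is this a detail left to an analysis plan: the article states the rule, so a later plan would have to reverse it.

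**Conclusion.** The point holds as a defect in a stated rule. Selection uses baseline tests that ignore the unit of randomisation and prognostic value, and entry is discretionary, so the adjustment set is neither fixed nor reproducible from the protocol. For covariate ICCs of 0.02 to 0.20, balanced variables are flagged about 1.4 to 4.5 times as often as the nominal 10%. These rates assume 10 patients per practice and do not allow for stratification by practice size, which would lower them for characteristics linked to size.

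The consequence is moderate. No inflation of type I error by the rule itself was shown, and the group-by-time contrasts are almost unaffected. What is lost is a fixed model, plus some precision where arm levels are compared. Choice among more than two models was not simulated.

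**What to change.** 1. Delete the baseline significance tests and the p≤0.10 rule. Report baseline data by arm descriptively.
2. Replace the discretionary sentence with a fixed set: age, sex and the practice-size stratum used in randomisation, alongside the disease term already in the model, whatever the observed balance.
3. State how t0 activity is used. Either keep t0 as a response and do not also adjust for it, or model t1 and t2 as outcomes with t0 PAM minutes as a covariate. Using it in both roles puts the same measurement on both sides of the model.
4. Because patients consent after allocation is known, allow adjustment for further variables only as a labelled sensitivity analysis that does not replace the primary result.

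Cost: items 1, 2 and 4 are wording changes. Age and sex take two degrees of freedom at patient level. Four size strata take three at practice level, leaving 24 − 3 − 3 = 18 instead of 21. If t0 becomes a covariate, the model needs a small re-specification.

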#### Data analysis for primary and secondary outcomes

An intention to treat analysis and a per protocol analysis will be conducted. For each outcome measure (all outcomes are continuous) data will be expressed as mean +/-SD. The between group comparisons will be analysed with multilevel analysis to account for the dependency of observations. We will apply a 3 level linear mixed model (time, participant, practice); the level of statistical significance will be set at 0.05 (two-tailed). Separate models (random intercept) will be set up for each outcome measure. The independent variables in each model are two dummy variables indicating the group, with the group of patients receiving usual care as the reference category and two dummy variables for time and their interaction effects. In addition, an extra dummy variable will be included to indicate the patient group (COPD versus DM2), to study whether the effects in COPD patients differ from the effects in patients with DM2. If needed, additional baseline variables will be included to account for possible confounding. If normality assumptions are violated, outcome variables will be log-transformed and if necessary non-parametric tests will be used. SPSS, version 19 and Mlwin, version 2.02 will be used to analyse the data.

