##### Sample size and power calculation

For this study, 240 patients are required, with a minimum of 80 participants per group. Based on a validation study, we assume that the PA level of participants is an average of 24 minutes with a range of 14.6 minutes. A mean difference between group 1 and group 3 of ten minutes (42 %) of moderate to vigorous PA spent per day will be seen as clinically relevant. While assuming an intra-class correlation of 10 % based on practice, to account for the dependency of the data, with a power of 80 % and a significance level of 0.05, a total of 72 patients over 8 general practices are required in each group. Because a drop-out rate of 10 % is expected, practices will be asked to include 8–14 patients per practice in each subgroup, depending on the size of the practice.

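### The random-intercept model leaves practice-level variation in change out of the group-by-time test, so its type I error can exceed 5% by an amount the protocol cannot bound

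*Protocol article*

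**What the plan says.** Under *Data analysis for primary and secondary outcomes*, the Protocol article plans a linear mixed model with three levels: occasion, patient and practice. The random part is fixed by one sentence: "Separate models (random intercept) will be set up for each outcome measure". The fixed part has two group dummies (usual care as reference), two time dummies and their interactions. A dummy for COPD versus diabetes is added. No practice-by-time effect or random slope is mentioned.

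The same paragraph gives a fallback: "If normality assumptions are violated, outcome variables will be log-transformed and if necessary non-parametric tests will be used". The tests are not named.

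Three other places bear on this:
- *Sample size and power calculation* allows for clustering, "assuming an intra-class correlation of 10 % based on practice". It does not say whether this ICC refers to activity levels or to change.
- *Randomisation procedure* allocates whole practices, eight per arm.
- *Process evaluation* says the investigators expect practice nurses to differ widely in how they carry out the intervention.

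**The concern.** *Objectives and hypotheses* describes an increase in activity that is then maintained, and baseline is one of the modelled outcomes. Read together, these make the group-by-time interaction the test of the intervention. That interaction is a within-patient contrast.

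A random intercept for practice describes practices that differ by the same amount at every occasion. Such differences cancel when baseline is subtracted. What matters for the interaction is whether patients of one practice tend to change together, and a model with intercepts only has no term for that. Its residual then treats the changes of patients in one practice as independent.

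If change does cluster by practice, the confidence interval for the primary comparison is too narrow and the stated 0.05 level is not kept. The sample size would have been enlarged for clustering while the main test makes no allowance for the part of it that affects change.

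**Working it through.** **Inputs from the protocol.** Two-sided alpha 0.05; power 80%; target difference 10 minutes; 14.6 minutes, printed in "an average of 24 minutes with a range of 14.6 minutes" and read here as a standard deviation; practice ICC 0.10; 72 patients over 8 practices per arm, so m = 9 per practice; 80 per arm after 10% dropout, so m = 10.

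**Inputs the protocol does not give.** The practice-level ICC of change, ρ, taken from 0 to 0.10; for the illustration in minutes, a correlation of 0.6 between occasions within patients.

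**Step 1: the plan's own figure.** Without clustering, n = 2 × [14.6 × (1.960 + 0.842) / 10]² = 33.5, so 34 per arm. The design effect at m = 9 is 1 + 8 × 0.10 = 1.8, and 34 × 1.8 = 61.2, which is below 72. A practice-level t test with 9 patients per practice has 74.9% power with 7 practices per arm and 81.3% with 8 (14 degrees of freedom). Eight practices, or 72 patients, is thus the smallest number that reaches 80%, and 72 / 0.9 = 80. The stated size is consistent with an analysis in which practice variance counts fully against the comparison.

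**Step 2: the interaction.** Let s_e be the patient-level residual variance per occasion, s_pt the practice-by-time variance, k practices per arm and n = k × m. With complete data:
- True variance of the difference in change: 2 × (2 s_e / n + 2 s_pt / k)
- Variance the random-intercept model reports, approximately: 2 × 2 (s_e + s_pt) / n
- Ratio: (s_e + m s_pt) / (s_e + s_pt) = 1 + (m − 1)ρ, with ρ = s_pt / (s_e + s_pt)

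The time-constant practice variance appears in neither line. The actual type I error is 2 × [1 − Φ(1.96 / √ratio)].

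| ρ | Ratio, m = 9 | Type I, m = 9 | Ratio, m = 10 | Type I, m = 10 | Simulated, m = 9 / 10 |
|---|---|---|---|---|---|
| 0 | 1.00 | 5.0% | 1.00 | 5.0% | 5.3% / 5.2% |
| 0.02 | 1.16 | 6.9% | 1.18 | 7.1% | 6.8% / 7.4% |
| 0.05 | 1.40 | 9.8% | 1.45 | 10.4% | 9.8% / 10.3% |
| 0.10 | 1.80 | 14.4% | 1.90 | 15.5% | 14.3% / 15.6% |

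Fitting the three-level random-intercept model itself (m = 9, about 900 simulated trials per setting) gave 4.5%, 9.8% and 15.2% at ρ = 0, 0.05 and 0.10. A practice-level analysis of change gave 4.7 to 5.6% throughout.

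**Step 3: illustration in minutes.** Take s_e = 0.9 × 14.6² × (1 − 0.6) = 76.7 and total practice variance 0.10 × 14.6² = 21.3.
- If 20% of the practice variance changes over time, s_pt = 4.26 and ρ = 4.26 / 81.0 = 0.05. The true standard error is 2.53 minutes against 2.12 reported, and type I error is 10.0%.
- If 50% does, s_pt = 10.66 and ρ = 10.66 / 87.4 = 0.12. The figures are 3.10 against 2.20, and 16.3%.

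**Step 4: variation only in groups 1 and 2.** In the group 1 versus group 3 contrast, s_pt now enters the true variance once, and the residual pooled over three arms is s_e + (2/3) s_pt.
- 20% case: true 4 × 76.7 / 72 + 2 × 4.26 / 8 = 5.33; reported 4 × 79.6 / 72 = 4.42; ratio 1.21; type I error 7.4%.
- 50% case: 6.93 against 4.66; ratio 1.49; 10.8%.

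**Step 5: the fallback, if an ordinary rank test were used.** With a level ICC of 0.10, an unclustered Mann-Whitney test of t1 values, group 1 against group 3, rejected in about 14 to 20% of simulated null trials. On change scores it rejected in about 5% at ρ = 0, 9% at 0.05 and 13 to 15% at 0.10.

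**The case against.** The strongest reply is that the plan does handle clustering: practice is a declared level, and the stated aim of the multilevel model is to deal with dependent observations. That stands. A reader might infer that clustering has been dropped from the analysis altogether, but the text does not support this. Stable differences between practices are modelled, and they do no harm to the change contrast. Only practice-by-time variation is missing.

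A second reply is that the inflation depends on an ICC of change that the protocol never states. If practice effects are stable, the planned test keeps 5%. That stands too. The 10% ICC in the sample size section is not said to apply to change, and the 16.3% case needs an ICC of change of 0.12, above that figure.

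Third, variable delivery by nurses can arise only in groups 1 and 2, which lowers the figures to those in Step 4. If the intervention did nothing in any practice, variable delivery would by itself create no variation in change. The process evaluation statement therefore bears at least as much on interval width as on false positives. This limits the size of the problem but does not remove it, since the interval is also part of the primary result.

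Fourth, a reader might infer that the non-parametric fallback ignores practice. The protocol names no test, and a condensed article may leave the choice to the analysis plan. Step 5 shows what an ordinary rank test would do, not what the plan says will be done.

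The reply that random-effects detail belongs in the analysis plan fails here, because the article itself fixes the random part.

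**Conclusion.** The point holds in a limited form. As specified, the standard error of the group-by-time contrast contains no allowance for practices that change by different amounts, although the design and the protocol's own expectations make such variation plausible.

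The consequence is conditional. With 9 to 10 patients in each of 8 practices per arm, the nominal 5% two-sided test has a true level from 5% (ICC of change 0) to about 14 to 16% (ICC 0.10), with about 7% at 0.02 and about 10% at 0.05. These figures assume balanced, complete data and equal practice-by-time variance in the compared arms; they are lower if only the intervention arms vary. It would be wrong to report 10 to 16% as the plan's error rate, because the protocol gives no ICC of change.

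**What to change.** In *Data analysis for primary and secondary outcomes*, replace the random-intercept specification by one of these:
- the same three-level model with an added practice-by-time random effect;
- a model of t1 and t2 with the patient's t0 minutes as covariate and practice-level random effects, so that practice variation at follow-up enters the contrast;
- a practice-level analysis of change.

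State small-sample degrees of freedom suited to eight practices per arm. Add that any non-parametric fallback must respect practice, for example by permuting practices within the randomisation strata.

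This changes analysis wording only and should be settled before the group variable is revealed. The cost is a somewhat wider interval if change does cluster: at m = 9, the true standard error exceeds the one the planned model reports by a factor of √1.40 = 1.18 at an ICC of change of 0.05 and √1.80 = 1.34 at 0.10. Small-sample degrees of freedom widen the interval a little further.

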### Data collection

All participants are asked (by a letter from the researchers) to wear the PAM and complete questionnaires at three different time points; namely at baseline (t0), at the end of the intervention after 4–6 months (t1), and at follow-up, 3 months after the end of the intervention (t2). Measurements and time points are summarised in Table 
2.

**Table 2 T2:** Measurements and time points

**Concept (questionnaires)**	**Intervention groups**			**Control group**		
	**t0**	**t1**	**t2**	**t0**	**t1**	**t2**
Demographic variables	x			x		
Physical activity (PAM)	x	x	x	x	x	x
Quality of life (SF 36)	x	x	x	x	x	x
General Self-Efficacy (GSS)	x	x	x	x	x	x
Exercise Self-Efficacy (ESS)	x	x	x	x	x	x
Health status (DSC-R or CRQ-SAS)	x	x	x	x	x	x
Process evaluation		x				

PAM: Personal Activity Monitor.

DSC-R: Diabetes Symptom Checklist-Revised.

CRQ-SAS: Chronic Respiratory Questionnaire-Self-Administered Standardised.

T0 - baseline.

T1 - after 4–6 months (end of intervention).

T2 - after 9 months (post intervention).

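### A random-intercept model for three unequally spaced visits makes the t0–t2 standard error too small if within-participant correlation falls with time

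*Protocol article*

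**What the plan says.** The section on data analysis for primary and secondary outcomes in the protocol article states: "We will apply a 3 level linear mixed model (time, participant, practice"). It continues: "Separate models (random intercept) will be set up for each outcome measure". The fixed effects are two group dummies with usual care as reference, plus "two dummy variables for time and their interaction effects". The treatment effects are therefore differences in change from t0 to t1 and from t0 to t2. For testing, "the level of statistical significance will be set at 0.05 (two-tailed"). The section names no random slope, serial residual, unstructured covariance or robust standard error.

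The data collection section puts t1 at the end of the intervention, after 4–6 months, and t2 three months after that. The notes to Table 2 say "T2 - after 9 months (post intervention"), and the abstract gives follow-up at 6 and 9 months. The main hypothesis, under objectives and hypotheses, covers both an increase over the intervention period and its maintenance over the next three months.

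**The concern.** A participant random intercept with independent residuals implies that a participant's t0 and t1 values are correlated exactly as strongly as the t0 and t2 values, and that the variance is the same at every visit. The model then uses one pooled residual variance for every change contrast. The t0–t2 pair is the furthest apart. If correlation weakens with time, that pair is less correlated than the average pair, and the pooled variance understates the true variance of its change. The interval for the t2 effect is then too narrow, and the maintenance claim is tested above the nominal level.

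Follow-up data will not be imputed, and the plan relies on the multilevel model to handle dropout (section on missing, unused and unexpected data). With incomplete follow-up, a wrong covariance can also move the point estimates. That part has not been quantified here.

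**Working it through.** **The plan's own figure.** The sample size section uses a 10-minute difference, practice ICC 0.10, "with a power of 80 % and a significance level of 0.05", and activity levels with "an average of 24 minutes with a range of 14.6 minutes". Taking 14.6 as the SD is an assumption, since the text calls it a range.
- Per arm without clustering: 2 x (1.960 + 0.842)² x 14.6² / 10² = 33.5, so 34.
- Design effect with 9 per practice: 1 + 8 x 0.10 = 1.8, giving 33.5 x 1.8 = 60.2 by the normal approximation.
- With a t-test on practices (14 df for 8 + 8), 7 practices per arm give 74.9% power and 8 give 81.3%. That yields 8 x 9 = 72, as stated, and 72 / 0.90 = 80.

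The stated size therefore reproduces from a single-time comparison. No within-participant correlation enters it.

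**Standard error of the change contrasts.** Let r01, r12 and r02 be the within-participant correlations. None is in the documents, so all values below are assumptions. With complete balanced data and equal variances:
- the random-intercept model's variance of either change from t0 is proportional to 1 − mean(r01, r12, r02);
- the true variance is proportional to 1 − r01 at t1 and 1 − r02 at t2;
- k = model SE / true SE = √[(1 − mean r) / (1 − r)], and type I error = 2 x [1 − Φ(1.96 k)].

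**(a) Equal adjacent correlations, t0–t2 lower by 0.1 or 0.2**

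| r01 = r12 | r02 | mean r | k at t2 | type I, t2 | k at t1 | type I, t1 |
|---|---|---|---|---|---|---|
| 0.6 | 0.5 | 0.567 | 0.931 | 6.8% | 1.041 | 4.1% |
| 0.6 | 0.4 | 0.533 | 0.882 | 8.4% | 1.080 | 3.4% |
| 0.7 | 0.6 | 0.667 | 0.913 | 7.4% | 1.054 | 3.9% |
| 0.7 | 0.5 | 0.633 | 0.856 | 9.3% | 1.106 | 3.0% |
| 0.8 | 0.7 | 0.767 | 0.882 | 8.4% | 1.080 | 3.4% |
| 0.8 | 0.6 | 0.733 | 0.816 | 11.0% | 1.155 | 2.4% |

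Worked row for 0.7 / 0.5: √[(1 − 0.633) / (1 − 0.5)] = √0.733 = 0.856; 1.96 x 0.856 = 1.678; two-sided tail 9.3%.

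**(b) Exponential decay in real time, 9-month correlation 0.4–0.7**

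| t1, t2 (months) | type I, t1 | type I, t2 |
|---|---|---|
| 6, 9 | 5.2–5.5% | 9.3–10.3% |
| 5, 8 | 4.5–4.8% | 9.4–10.3% |
| 4, 7 | 3.7–4.0% | 9.5–10.4% |
| 4, 9 | 1.9–2.4% | 9.2–10.2% |

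Adding a stable person component to the decay (visits at 6 and 9, 5 and 8, or 4 and 7 months) gives 4.4–5.5% at t1 and 6.3–7.4% at t2.

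**(c) Simulation.** 20,000 trials of 3 arms x 8 practices x 10 participants:
- r = (0.6, 0.6, 0.6): 5.2% at t1 and 5.0% at t2;
- r01 = r12 = 0.7, r02 = 0.49: 2.9% and 9.8%;
- r01 = 0.63, r12 = 0.79, r02 = 0.50 (decay at 6 and 9 months): 5.3% and 10.0%.

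**(d) In minutes.** Take 80 per arm, SD 14.6 and 10% of the variance between practices, so the within-practice variance is 0.9 x 14.6² = 191.8. For the 6- and 9-month pattern in (c), mean r = 0.641.
- Model SE: √(2 x 0.359 x 191.8 x 2/80) = 1.85 min for both contrasts.
- True SE at t1: √(2 x 0.37 x 191.8 x 2/80) = 1.88 min.
- True SE at t2: √(2 x 0.50 x 191.8 x 2/80) = 2.19 min.

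The reported 95% half-width at t2 would be 1.96 x 1.85 = 3.6 min where 1.96 x 2.19 = 4.3 min is correct.

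**The case against.** **The text is condensed.** The random intercept appears in a parenthesis in a journal article, and a random intercept can be combined with a serial or heterogeneous residual structure. Residual covariance is often left to the analysis plan. This has some weight: independence of the residuals is inferred, because the article does not state it. But the article does name the covariance device it will use and mentions no other, so the natural reading is a stated choice that can be tightened here.

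**The harm is conditional.** No correlation or visit-specific variance is given, and with equal correlations nothing goes wrong. With complete data the point estimates are unaffected. This stands and limits the finding.

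**Stronger readings that the documents do not support.** A reader might infer that both contrasts get wrong error bars. That needs r01 = r12 or an early t1. At 6 and 9 months with decay in real time, r01 lies close to the mean of the three correlations, and t1 is tested at 5.2–5.5%.

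A reader might also infer that the t1 test falls clearly below the planned 80% power. That 80% belongs to the single-time comparison reproduced above, not to a change contrast. Under the correlations in (a), with SD 14.6, 72 per arm and no practice-by-time variation, power for a 10-minute difference in change to t1 stays at about 99% or more with either standard error.

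**Conclusion.** The point holds for t2. Read naturally, the specified model imposes equal variances and equal correlations on three unequally spaced visits. In every decay pattern tried, the t0–t2 standard error is too small and type I error on the maintenance contrast is about 6–11% instead of 5% (6.8–11.0% over the range in (a)). With equal correlations it is 5%.

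At t1 the direction depends on timing: close to nominal at 6 and 9 months, conservative when t1 is early. No loss from the stated 80% power is claimed, and the 72 per arm stands.

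These figures rest on assumed correlations, equal variances, complete data, independent level-1 residuals and no practice-by-time variation. The change is worth making because the error at t2 runs in one direction under decay and the remedy is cheap.

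**What to change.** In the section on data analysis for primary and secondary outcomes, replace the participant-level random intercept with an unstructured 3 x 3 within-participant covariance over t0, t1 and t2, and keep the practice random effect.

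The unstructured form has six covariance parameters against two for a random intercept with one residual variance. The four extra are estimated from 240 participants. It contains the equal-correlation model as a special case, so little is lost if that model is true. If correlation does decay, the t2 interval becomes somewhat wider, as it should. No further data are needed, and the sample size does not change.
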